## Abstract

**Aim:** This study aims to build the capacity of the people at grass root level as gatekeepers of mental health. It will assess the effectiveness of the Gatekeeper Training Program (GTP) on gatekeeper behaviour, awareness, attitude, and mental help seeking intention.

**Design:** An evaluative research approach in two phases. Phase 1: Cross-sectional house-to-house exploratory survey. Phase 2: A quasi-experimental design with multiple follow ups at 0, 6 and 12 months.

**Method:** Data will be collected using standardized tools like Mental Health Knowledge Questionnaire (MHKQ), Community Attitude towards Mentally Ill (CAMIS), Mental Help Seeking Intention (MHSIS) and Gatekeeper Behavior Scale (GBS). For Phase 1, a house-to-house survey will be conducted among the selected colonies of Koraga tribe to determine their awareness, attitude, and mental help seeking intention regarding common mental health problems. Phase 2 includes identification of the leaders/representatives of the selected tribal colonies, and involving them in GTP. Pre-test and multiple post-test will be conducted in Phase 2 at 0, 6, 12 months.  The study is funded by Indian Council of Medical Research from 16 August 2021 for 3 years duration.

**Discussion:** Treatment gap in psychiatric disorders remains an issue of great concern. Evidence based research promotes task shifting approaches in dealing with mental health problems in the community. Capacity building programs like GTP for the underprivileged section of the society are important especially in low and middle income group of countries.

**Impact:** This need based GTP, will ensure mental health first aid in the society. Early identification of people with mental health problems at their doorsteps has huge impact on the prognosis of the illness, closing the treatment gap and stigma reduction.

## Introduction

Tribal communities in India cannot be classified as one homogenous group, as they vary at different levels of development and belong to other ethnic-lingual groups. There are around 42,48,987 tribal people in Karnataka, of whom 50,870 belong to the primitive group. This primitive group of the tribal population represents 6.95 percent of the total population of Karnataka. The Koraga tribe is one of the most backward tribes classified under Particularly Vulnerable Tribal Group (PVTG) as declared by the Government of India. This tribe is scattered over many districts of the State, particularly in Udupi and Dakshina Kannada. Their number is 14,794 as per the 2011 census. The occupation of the Koraga tribe is at the pre-agricultural stage of development, i.e., they are experts in basket weaving, which is the primary source of income, but presently majority of them work as daily wage laborers (
Pujar *et al.*, 2017). Poverty and illiteracy are the main problems in their community (
Roy *et al.*, 2015). They are the poorest among the scheduled tribes of Karnataka (
Nalinam, 2013); around 48.4% of Koraga population have a meager monthly income of Rs.2001-4000 (
Pujar *et al.*, 2017). Alcoholism is another threat to the mental well-being of the Koraga tribal members. Several studies have reported widespread alcoholism among Koraga men and women; they also indulge in smoking beedi (tobacco) and chewing betel leaves. They spend a significant portion of the paltry income, leaving very little for other day-to-day expenses (
Nalinam, 2013). Even after 72 years of Independence and 60 years of the abolition of the untouchability practice, primary health care delivery is still inaccessible to the most vulnerable, primitive population. Unfortunately, people from Koraga tribe are still the “untouchables among the untouchable” (
Balakrishnan & Sharma, 2012).

## Background

In the Toto tribe of the Sub-Himalayan region, the prevalence rate of mental illness was 48.97%, with depression being the highest (
Ghosh *et al.*, 2004). A recent study from the West Godavari district of Andhra Pradesh, predominantly comprising people from scheduled tribes, highlighted that 15% of the present generation of the tribal population was affected by common mental disorders like stress, depression, suicide risk, and anxiety (
Maulik *et al.*, 2017). According to National Health and Family Survey (NHFS) 3, 72% of tribal men aged 15-54 years were addicted to tobacco, and 50% of tribal men were addicted to alcohol (
Ministry of Health and Family Welfare & Ministry of Tribal Affairs, 2013). Psychosocial problems were also reported among high school children of the Mysuru region. About 23.7% of children in the tribal area had anxiety disorders, 1.6% had mood disorders, 3.2% had suicidality, and 2.2% were diagnosed with ADHD (
Pradeep *et al.*, 2018). Koraga, a particularly vulnerable tribal group of Udupi district has shown significant liver dysfunction due to chronic alcoholism among its population, irrespective of its gender. Most of the daily wages were spent on alcohol as evident by majority (75%) of them being alcoholics (
Mungli *et al.*, 2013). Several studies have found that in general there is a vast treatment gap when it comes to the accessibility of mental health services. Although there are several reasons for the same, lack of awareness and stigma towards mental illness and mentally ill people are the most prominent. A cross-sectional survey assessing the effectiveness of community mental health programs in a tribal area of South India revealed that the mean score on awareness regarding mental illness was 5.13±2.27 among its study population (
Yalsangi, 2011). However, contrary to this, the majority (64%) of people from Naga tribe could recognize the presence of a mental health problem in a depicted vignette (
Longkumer & Borooah, 2013). Another study on stigma in mental illness revealed that 38.5% of persons with severe mental illness (PSMI) were found poor, and this poverty was strongly associated with stigma related to mental illness (OR 2.60, 95% CI 1.27 to 5.31), and scheduled tribes (2.39, 1.39 to 4.08). Therefore, it was concluded that females or people from lower castes having severe mental illness were more at risk to be economically poor due to stigma related to mental illness (
Trani *et al.*, 2015).

The Systematic Medical Appraisal, Referral and Treatment (SMART) mental health project of Andhra Pradesh found that 7% of people go to faith healers and religious leaders at the very beginning of their mental illness for treatment (
Maulik *et al.*, 2017). The preference for magico-religious healing and traditional practices to overcome mental health concerns is prevalent in South-Asian countries, evidenced by a qualitative study from Bangladesh on tribal communities (
Rahman *et al.*, 2012). As mentioned earlier, the study poses a challenge to the healthcare delivery system in low-income countries, which mainly caters to the plainland population. A randomized controlled trial across 32 colleges of USA evaluated the effectiveness of the gatekeepers training program and found that trainees' self-perceived knowledge, ability, and confidence to identify students in distress were increased (
Lipson *et al.*, 2014). In the long-term effects of community gatekeeper training, 15 (n=40) participants had helped someone at risk of suicide; also, intentions to help and confidence to identify someone at risk of suicide remained high (
Deane *et al.*, 2006). Though common mental health problems are prevalent among the tribal population, as evident by the research studies mentioned above, very little is done to improve their condition in India. Hence, it is vital to improve the mental health care system for our most primitive and underprivileged tribal people and develop effective mental health care programs at the grassroots level.

**Aims and Objectives:** The objectives of the study are to:
•Determine the awareness, attitude and mental help seeking intention regarding common mental health problems among the tribal population using standardized tools.•Assess the awareness, attitude, mental-help seeking intention and gatekeeper behavior among the leaders/representatives of Koraga tribe regarding common mental health problems using standardized tools.•Find out the effectiveness of gatekeeper training program on awareness, attitude, mental help seeking intention and gatekeeper behavior among the leaders/representatives of Koraga tribe regarding common mental health problems.•Determine the number of vulnerable individuals identified, counselled, referred to a tertiary center as and when needed by the trained gatekeepers of the tribal community at 12 months of follow up.

## Methods

### Research approach and design

The study is based on an evaluative approach to meet its objectives. The study will be done in two phases. Phase 1 will be a cross-sectional house-to-house survey where data will be collected from the Koraga tribe and Phase 2 will have a quasi-experimental design which includes an experimental and a control group. There will be pre-test and post-test for both the groups with multiple follow ups at 0, 6 and 12 months. GTP (intervention) will be carried out only for the experimental group.

### Setting and population

The study will be conducted in Koraga tribal colonies of Udupi district, Karnataka. There are around 360 colonies spread across seven blocks of the Udupi district, and each colony comprises a minimum of 8-10 families. The colonies are geographically distinct in nature. The total Koraga population is 11,133 in Udupi district. Variables under Phase 1 of the study will be awareness, attitude, and mental help seeking intention and Phase 2 variables include awareness, attitude, mental help seeking intention and gatekeeper behavior regarding common mental health problems.

### Sampling technique

Phase 1: Based on convenient sampling technique, out of the seven blocks, three blocks will be taken up for the survey. Each of these three blocks comprises a minimum of 35 colonies, hence 25-27 colonies will be selected randomly from each block. Stratified sampling technique (age and gender) will be used to select five samples/colony for the survey.

For phase 2, convenient sampling technique will be used to select the block (largest block) for experimental and control group. These largest blocks consist of 85-90 colonies, hence 55 colonies will be selected randomly. Further purposive sampling technique will be used to select the participants for GTP (
Figure 1: Schematic representation of sampling technique).

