### Sample size

Phase 1 sample size is calculated using the formula as mentioned below. In this formula the confidence level is 95%, hence Z
^2^ = 1.96. Here proportion of the tribal people having awareness regarding common mental health problems was assumed to be 0.5 and (d) is the precision of the study (corresponding to the effect size) = 0.05.

$$n=\frac{Z^{2}P\;\left(1-P\right)}{d^{2}}=384\approx 400$$

For Phase 2: Using G* power software the sample size was estimated to be 86 (43 in each group).

With 20% attrition rate n = 108 (54 in each group).

(Here the values are as follows: Effect size = 0.25, Alpha error = 0.05, power = 0.8, Number of groups = 2, Number of measures = 3.)

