**Ethical consideration:** Permission to conduct the study is received from the Head of the Institution, Institution Review Committee and Institutional Ethics Committee (322/2020). Permission is also obtained from the tribal community authority (Integrated Tribal Development Office) at the district government office of Udupi. This study is registered in Clinical Trial Registry of India (CTRI/2021/06/034037 [Registered on: 07/06/2021]. Informed consent will be obtained from all participants, and a complete explanation of the investigation will be provided.

Participation in this study is voluntary; the participants may decline to participate at any time, and they need not give any reason for the same, and such withdrawal shall be without penalty. If they withdraw from the study before data collection is completed, the data collected until they indicated withdrawal will be used in the study report. The sample size is calculated by keeping in mind the attrition rate at 20%, hence the sample size will not be affected with the drop-outs.

**Data analysis:** Demographic characteristics of the study participants will be presented in descriptive summary tables. The outcome variables across the follow up period will be analyzed by repeated measures of ANOVA. The categorical variables will undergo bivariate analysis by applying the Chi-square test for categorical variables. A p-value of less than 0.05 will be considered the criteria for statistical significance. Overall SPSS 26 version will be used to analyse the data gathered.

**Dissemination of results:** The results will be disseminated via presentations at appropriate scientific conferences and workshops. The findings will also be published in peer-reviewed journals, professional and institutional repositories etc. The result will be discussed with the Department of Tribal Welfare and other stakeholders for improvement of mental health awareness, accessibility to meantal health care and appropriate utilization of community-based resources.

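### Phase 1's 5-point precision is not assured: the sample size formula assumes simple random sampling, but the survey takes five people per colony

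*Protocol article*

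**What the plan says.** In the protocol article, Sample size, Phase 1 uses n = Z²P(1−P)/d² and arrives at 384, rounded up to 400. The inputs are 95% confidence, an assumed value for the "proportion of the tribal people having awareness regarding common mental health problems was assumed to be 0.5", and a margin described as "d) is the precision of the study (corresponding to the effect size) = 0.05". No design effect or intracluster correlation (ICC) appears.

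Sampling technique describes a multistage sample. Blocks are chosen by convenience: "out of the seven blocks, three blocks will be taken up for the survey". Then: "Each of these three blocks comprises a minimum of 35 colonies, hence 25-27 colonies will be selected randomly from each block". Finally, stratification by age and gender "will be used to select five samples/colony for the survey". The same section says that the largest blocks, used for Phase 2, have 85–90 colonies. It does not say whether those blocks are among the three surveyed.

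The Data analysis paragraph states: "The categorical variables will undergo bivariate analysis by applying the Chi-square test for categorical variables". It does not tie this test to Phase 1.

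**The concern.** The formula treats 400 answers as independent, but the design takes five people from each of roughly 80 small, geographically separate colonies. People in one colony are likely to resemble each other in awareness, attitude and help-seeking intention. Any such resemblance means that 400 people carry less information than 400 independent respondents.

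The low end of the colony range also yields fewer people than the plan's own calculation requires. In addition, taking the same number of colonies from blocks of different size, and the same number of people from colonies of different size, gives people unequal chances of selection.

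Describing awareness, attitude and help-seeking intention in the tribal population is the study's first objective, and the knowledge gaps found in Phase 1 feed the training module. At stake are the precision claimed for those descriptive figures and the population they describe. The Phase 2 test of the training programme is not affected.

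**Working it through.** **Inputs.** From Sample size: Z = 1.96, P = 0.5, d = 0.05. From Sampling technique: 3 blocks, 25–27 colonies per block, 5 people per colony, at least 35 colonies in each surveyed block, 85–90 in the largest blocks. From Setting and population: 360 colonies and 11,133 people in the district. The documents give no ICC, so a range is assumed.

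**The plan's figure.** 1.96² × 0.5 × 0.5 / 0.05² = 384.16, so 384 reproduces. The text prints 1.96 as the value of Z². Taken literally that would give 1.96 × 0.25 / 0.0025 = 196, so it is a slip of notation and was not the value used.

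**Yield of the sampling plan**, with half-width 1.96 × √(0.25/n) under the plan's own formula:

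| Colonies per block | People | Half-width (points) |
|---|---|---|
| 25 | 3 × 25 × 5 = 375 | 5.06 |
| 26 | 3 × 26 × 5 = 390 | 4.96 |
| 27 | 3 × 27 × 5 = 405 | 4.87 |

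The target of 400 needs 400/5 = 80 colonies, for example 27 + 27 + 26, which lies inside the stated range.

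**Clustering.** The design effect is DE = 1 + (5 − 1) × ICC = 1 + 4 × ICC. The half-width at n = 400 is 1.96 × √(0.25 × DE/400).

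| Assumed ICC | DE | Effective n (400/DE) | Half-width (points) | n needed for 5 points (384.16 × DE) |
|---|---|---|---|---|
| 0.01 | 1.04 | 385 | 5.0 | 400 |
| 0.02 | 1.08 | 370 | 5.1 | 415 |
| 0.05 | 1.20 | 333 | 5.4 | 461 |
| 0.10 | 1.40 | 286 | 5.8 | 538 |

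The ICC at which 400 people just give 5 points is (400/384.16 − 1)/4 = 0.010. For 405 people it is (405/384.16 − 1)/4 = 0.014.

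**Inference limited to the three blocks.** The design effect above treats colonies as drawn from a very large supply. If the target is only the three blocks, a large fraction of their colonies is sampled and the between-colony part of the variance shrinks. The two-stage variance is

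V = (1 − f₁) × S₁²/k + (1 − f₂) × S₂²/(k × m),

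with k = 80 colonies, m = 5, S₂² = 0.25 × (1 − ICC), S₁² = 0.25 × ICC + S₂²/M, f₁ = 80/(3 × colonies per block) and f₂ = 5/M. M is taken as 11,133/360 = 30.9 people per colony. This is an assumption: it counts all ages and treats colonies as equal in size.

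- At 35 colonies per block, f₁ = 80/105 = 0.76. The half-width is 4.6 points at ICC 0.05 and 4.7 at ICC 0.10.
- At about 87 colonies per block, f₁ = 80/261 = 0.31. The half-width is 5.1 points at ICC 0.05 and 5.4 at ICC 0.10.

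**Selection probabilities.** With 25 colonies drawn, a colony in a block of 35 has a chance of 25/35 = 71%. In a block of 90 it would be 25/90 = 28%, if a block that large is among the three. Within a colony the chance is five divided by the number of eligible adults, so it falls as the colony grows. Unweighted percentages therefore over-represent people in small colonies and in blocks with few colonies.

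**The case against.** A reader might infer that Phase 1 fails to deliver its stated precision. The documents do not support that.

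- **The count.** The figure of 375 is only the bottom of a stated range. The plan's target is 400, which 27 + 27 + 26 colonies reach exactly. Even at 375 the miss is 0.06 of a point. A finite-population correction for 11,133 people would lower the requirement to 384.15/(1 + 383.15/11,133) ≈ 371, although the plan does not invoke one. This stands, and the count is a secondary inconsistency.
- **The ICC.** It is assumed, and with inference confined to the three blocks the high sampling fraction can keep the margin below 5 points. This also stands. It makes the conclusion conditional but does not remove it: the actual block sizes are not given, and the objective speaks of the tribal population, not three blocks.
- **The test.** A reader might also infer that Phase 1 p-values will be too small because an ordinary chi-square test is named. That test is not tied to Phase 1, a cluster adjustment could sit in an analysis plan that is not shown, and comparisons by age or gender are largely within colonies, where ignoring clustering need not inflate significance. This point is supporting only.
- **Condensed article.** Analysis detail can be left to a fuller document. The sample size calculation, however, is stated in the article, and it does not match the design stated beside it.

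**Conclusion.** The point holds in a conditional form: 5-point precision is not assured. Under the usual design effect, the rounding from 384 to 400 covers a colony ICC of only about 0.01, and at assumed ICCs of 0.02–0.10 the half-width is about 5.1–5.8 points. For the three blocks alone it lies between about 4.6 and 5.4 points at ICC 0.05–0.10, depending on block size and on the assumption of about 31 people in equal-sized colonies. The loss is therefore at most moderate over this range.

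Unequal selection follows from the sampling text and needs no ICC. How far it biases the results cannot be computed, because colony and block sizes are not given and the bias depends on whether answers vary with size. The low end of 375 should be reconciled with 384 and 400, but it matters little by itself. The change is worth making before data collection, which the Study status section says has not begun. Nothing here invalidates the survey.

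**What to change.** 1. In Sampling technique, set a minimum of 80 colonies in total (for example 27 + 27 + 26), so that the yield is at least 400.
2. In Sample size, state the design effect and an ICC range. Give the Phase 1 precision as conditional on that range and on whether inference is to the three blocks or to the wider tribal population. Correct the printed value of Z².
3. Record the number of colonies in each surveyed block and of eligible adults in each sampled colony. Report Phase 1 estimates with block as stratum, colony as cluster and inverse-probability weights. Where a chi-square test is used on Phase 1 data, use a design-based version such as Rao–Scott.
4. Describe the results as applying to the three selected blocks, since these are chosen by convenience.

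Cost: up to 400 − 375 = 25 more interviews than the low end of the range, all within the planned 25–27 colonies per block. There is also slightly more analysis work, and the stated precision becomes slightly less favourable.

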**Figure 1. f1:**
[figure not shown]
Schematic representation of sampling technique.

### Sample size

Phase 1 sample size is calculated using the formula as mentioned below. In this formula the confidence level is 95%, hence Z
^2^ = 1.96. Here proportion of the tribal people having awareness regarding common mental health problems was assumed to be 0.5 and (d) is the precision of the study (corresponding to the effect size) = 0.05.

$$n=\frac{Z^{2}P\;\left(1-P\right)}{d^{2}}=384\approx 400$$

For Phase 2: Using G* power software the sample size was estimated to be 86 (43 in each group).

With 20% attrition rate n = 108 (54 in each group).

(Here the values are as follows: Effect size = 0.25, Alpha error = 0.05, power = 0.8, Number of groups = 2, Number of measures = 3.)

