### Intervention

Gatekepeer Training Program (GTP) is a two-day mental health workshop.

The content for the workshop (module) is being prepared by the primary investigator. Knowledge gap observed from phase 1 (survey) of the study is included in the module. This module will be given to a panel of experts in various fields of psychiatry at local, national, and international level. The suggestions and modifications will be incorporated accordingly.

The program will be implemented by the same multi-disciplinary team members in various community locations as per the convenience of the participants or at a single location if all participants (54) could meet up conveniently.

The investigator will be in contact with the participants throughout the post-intervention period to review/clarify the issues faced by the gatekeepers, and a diary will be provided to the participants in which they will have to document the details of interactions (if they had) with people having mental health concerns. (The sessions for the two-days workshop is listed in
Table 1.) The control group in the study will receive a module on the theoretical concepts of common mental health problems and gatekeeper behaviour. For both the experimental and control group, post-test will be conducted at three points of time i.e., at 0, 6, 12 months. After the follow-up duration of one year, a half-day workshop will be conducted for the control group at various community locations (as per the convenience of the participants). This workshop will focus on the theoretical concepts of the module provided earlier.

**Table 1. T1:** Outline of the two-day workshop on GTP.

Sl	Topic	Time	Resource person

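### The Phase 2 figure of 86 appears to be sized on a group main effect that does not isolate the training effect; the effectiveness test should use the pre-test, and the power should be restated for that test

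*Protocol article*

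**What the plan says.** The Sample size section of the protocol article gives 86 participants for Phase 2 (43 per group) from G*Power, raised to 108 (54 per group) for 20% attrition. The listed inputs are "Effect size = 0.25, Alpha error = 0.05, power = 0.8, Number of groups = 2, Number of measures = 3". The section does not say which repeated-measures test was chosen, what correlation between measures was assumed, or whether the pre-test is one of the three measures.

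The measurement schedule appears elsewhere. Under Research approach and design: "There will be pre-test and post-test for both the groups with multiple follow ups at 0, 6 and 12 months". Under Intervention, for both groups: "post-test will be conducted at three points of time i.e., at 0, 6, 12 months". Together these give one pre-test and three post-tests.

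Under Sampling technique, the Phase 2 blocks are chosen by convenience and the participants purposively, so the groups are not randomised. The third objective is to establish how effective the training is on the four outcomes. The Data analysis paragraph says: "The outcome variables across the follow up period will be analyzed by repeated measures of ANOVA". It does not say whether the group effect, the time effect or their interaction answers that objective.

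**The concern.** A power statement is useful only if it belongs to the test that answers the trial's question. In a non-randomised design with a pre-test and post-tests, that question is whether the groups differ after training, allowing for where each started. The figure of 86 appears to come from a different test: the difference between groups averaged over all repeated measures.

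That test has a fault whichever way the three measures are read. If the pre-test is among the averaged measures, the average includes an occasion on which training cannot yet have had an effect. If only the post-tests are averaged, any difference between the groups before training counts as a training effect.

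The printed 80% could therefore lead the trial to report either a diluted or a confounded comparison as its effectiveness result, although pre-test data that allow a better comparison are already planned.

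**Working it through.** **Inputs from the Sample size section.** "Effect size = 0.25" (read as Cohen's f, so d = 2f = 0.5 SD for two equal groups), "Alpha error = 0.05", power 0.80, "Number of groups = 2", "Number of measures = 3", N = 86.

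**Assumptions, not in the protocol.** The correlation ρ between any two measures is the same throughout (compound symmetry). It is shown at 0.3, 0.5 and 0.7.

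**Step 1: reproduce 86.** For m measures, the between-groups main effect has noncentrality λ = f²·N·m / [1 + (m−1)ρ], tested on F(1, N−2).
- m = 3, ρ = 0.5, N = 86: λ = 0.0625 × 86 × 3 / 2 = 8.06, power 0.801. At N = 85 power is 0.797, so 86 is the smallest N that reaches 0.80.
- The group × time interaction, λ = f²·N·m / (1−ρ), needs only N = 28 with the same inputs and ρ = 0.5. It needs 38 at ρ = 0.3 and 54 at ρ = 0. Other effect-size conventions for the interaction give 82, 156 or 158.
- The interaction matches 86 only with ρ = 0 together with a non-sphericity correction of 0.5, where the two formulas coincide. That is implausible, though not excluded.
- Attrition: 86 / 0.8 = 107.5, giving 108; 43 / 0.8 = 53.75, giving 54. Both agree with the protocol.

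The stated figure also depends on the unstated correlation. With three measures and N = 86, power is 0.88 at ρ = 0.3 and 0.73 at ρ = 0.7.

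**Step 2: three measures or four.** The same main-effect formula with m = 4 and ρ = 0.5 needs N = 82, and power at 86 is 0.826. The count alone does no harm.

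**Step 3: power at 86 for tests on the actual schedule.** Assume a group difference of 0 at pre-test and 0.5 SD at each of the three post-tests, with 43 per group. For a single contrast, λ = δ² / (v × 2/43), where δ is the expected contrast and v its variance in SD² units.
- *Main effect over four measures:* δ = (0 + 3 × 0.5)/4 = 0.375, v = (1 + 3ρ)/4. At ρ = 0.5, v = 0.625 and λ = 4.84.
- *Main effect over post-tests only:* δ = 0.5, v = (1 + 2ρ)/3. At ρ = 0.5, v = 2/3 and λ = 8.06.
- *Mean post-test minus pre-test:* δ = 0.5, v = (1−ρ)(1 + 1/3). At ρ = 0.5, v = 2/3 and λ = 8.06, the same as the line above.
- *Omnibus group × time, four measures:* λ = (43/2) × (3 × 0.125² + 0.375²) / (1−ρ), on F(3, 252). At ρ = 0.5, λ = 8.06.
- *Mean post-test adjusted for pre-test:* δ = 0.5, v = (1 + 2ρ)/3 − ρ², error df 83. At ρ = 0.5, v = 0.417 and λ = 12.9.
- *12-month score adjusted for pre-test:* δ = 0.5, v = 1 − ρ², error df 83. At ρ = 0.5, v = 0.75 and λ = 7.17.

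| Test at N = 86 | ρ = 0.3 | ρ = 0.5 | ρ = 0.7 |
|---|---|---|---|
| Group main effect, pre-test included | 0.70 | 0.58 | 0.50 |
| Group main effect, post-tests only | 0.88 | 0.80 | 0.73 |
| Omnibus group × time | 0.49 | 0.65 | 0.88 |
| Mean post-test minus pre-test | 0.66 | 0.80 | 0.95 |
| Mean post-test adjusted for pre-test | 0.93 | 0.94 | 0.98 |
| 12-month score adjusted for pre-test | 0.67 | 0.75 | 0.89 |

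The two adjusted rows assume no baseline imbalance between the groups.

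**The case against.** The strongest reply is that the arithmetic is right and the sample size may be adequate. Both 86 and 108 reproduce. If the three measures are the three post-tests, which fits the Intervention section, power is 0.80 at correlation 0.5, as printed. The direct one-degree-of-freedom test of change from pre-test to mean post-test also has exactly 0.80 there. All of this stands. On the post-tests-only reading the fault is exposure to bias, not loss of power.

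A reader might go further and infer that the trial is underpowered, or that any test of change from pre-test falls short of 80%. The protocol does not support that. Depending on the test and the correlation, power lies on either side of 80%, and the omnibus interaction rises from 0.49 to 0.88 over the range shown. If f = 0.25 were meant as the interaction effect itself, power at 86 would exceed 0.99. A reader might also treat three versus four measures as an error that invalidates the calculation, but four measures would need fewer participants.

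Two further points stand in part. The main-effect test is inferred, because the protocol does not name it. And the choice of test within a repeated-measures ANOVA is often left to an analysis plan. But the article prints a power calculation, and the test that reproduces it does not isolate the training effect on the printed schedule. How to use the pre-test is also debatable in non-randomised groups: covariate adjustment and change scores can disagree when baselines differ. That leaves open which pre-test-based analysis is chosen; it does not justify ignoring the pre-test.

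**Conclusion.** The point holds at moderate severity. On the most plausible reconstruction, the printed 80% is the power of a group main effect over three measures at an unstated correlation of 0.5. In this design that effect is either diluted by the pre-test (power about 0.50 to 0.70 at 86 completers) or unprotected against baseline differences (power 0.80 at correlation 0.5). A comparison that uses the pre-test avoids both faults. In the form of an adjusted mean of the post-tests it has 0.93 to 0.98 power from the same participants.

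These figures rest on a 0.5 SD difference at every post-test, none at pre-test, equal correlations of 0.3 to 0.7, and 43 completers per group. An effect that fades by 12 months, or groups that differ at pre-test, would change them. The result does not show that 86 or 108 is too few.

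**What to change.** Make three changes to the Sample size and Data analysis text:

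1. State that each Phase 2 participant is measured four times: pre-test, then 0, 6 and 12 months.
2. Name the effectiveness test for each tool as a group comparison of the post-tests that uses the same tool's pre-test, for example the mean of the three post-tests adjusted for pre-test, with a pre-specified adjusted contrast at 12 months. Say that the group main effect over all measures is not the effectiveness test.
3. Replace the power statement with the power of the named test at 86 completers. Write down the assumed correlation, show a range such as 0.3 to 0.7, and state the assumption of no baseline imbalance.

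Keep 108 recruited. The cost is rewording only, with no added participants, visits or instruments, and the Study status section says data collection has not begun. The one unwelcome consequence is that power for the 12-month contrast alone may be printed below 80% (0.67 at correlation 0.3, 0.75 at 0.5).
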